## Introduction

Breast cancer is a major public health challenge in Nigeria with an incidence of 52/100,000 [1], three-fold higher than the incidence four decades ago. Breast cancer incidence is projected to continue to increase in the coming decades. More worrisome, however, is the pattern of presentation–up to 80% of breast cancer cases in Nigeria present in advanced stages [2, 3]. This contributes significantly to high breast cancer mortality rates. This pattern of late presentation has remained unchanged over the last three to four decades [4]. Consequently, when combined with limited access to treatment overall, breast cancer survival in Nigeria is poor compared to high-income countries (HICs) [5–7]. Given the projected rise in breast cancer incidence, there may be an epidemic of advanced breast cancer cases without effective intervention in the coming years [8]. In addition to some recognized biological factors accounting for aggressiveness, it is clear that correctible epidemiological and system-related factors play major roles in late-stage presentation [9]. Both patient and system-related factors contribute significantly to delayed presentation [10]. Delayed presentation and lack of access to diagnostic and treatment facilities are recognized principal factors accounting for poor outcomes in low-middle-income countries (LMICs) [11, 12]. Patient-related factors include lack of breast cancer knowledge, fear of a cancer diagnosis and treatment, use of traditional and alternative remedies, and financial constraints. Awareness creation, community education, and advocacy to address erroneous patient beliefs must therefore form the basis of any early detection program. In addition, a lack of accessible breast cancer screening and the absence of a clearly defined clinical pathway for evaluating women with breast masses, coupled with limited access to diagnostic and treatment facilities, are key system factors requiring intervention [13].

Currently, there are no local data to support a specific breast cancer screening model in Nigeria. Developing a successful breast cancer screening program in a resource-limited setting requires substantial logistical and cultural considerations. Although mammography is recommended as the gold standard based on data from HICs, there are personnel, financial, and infrastructural challenges that limit its applicability for routine use in Nigeria [14].

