#### Sample size of cases

The sample size of 4100 study participants anticipated in the intervention arm (Ife North LGA) will include both asymptomatic (40–70 years) and symptomatic (30–70 years) women that will undergo screening and diagnostic evaluations respectively. In any screening exercise, there will be symptomatic cases that will use the opportunity of screening to present for evaluation. We anticipate a CDR of at least 3.5%. This expectation is supported by our previous publication of a mixed screening and diagnostic population in this geographic region demonstrating a breast CDR of 3.5% [19]. The CDR in this study will be the number of cancers detected among all study participants, including both the symptomatic and screening arms.

Our previous data demonstrate that the mean breast tumor size from an entirely symptomatic population at OAUTHC was 10.5 cm. This is much larger than findings from our recent study from the same region which included a screening population which demonstrated an average breast cancer size of 3.3 cm [19, 22]. We therefore project that cancers in the intervention community will be follow a similar pattern.

The primary outcome measure in this study is the stage at diagnosis. To achieve this, we projected the number of cases needed to detect a difference in the proportion of cases based on stage at diagnosis between the two study arms. From our preliminary data of 25 staged cancers, there were 7 (7/12, 58.3%) and 2 (2/13, 15.38%) stage IV cancers in the control and intervention arms respectively, with a 43% difference between the two groups. In order to detect a 43% difference in stage IV diagnoses between the two study arms with 80% statistical power at an alpha of 0.05, 23 cases will be needed in each arm. Our preliminary data show 13 total cancer cases detected in 791 patients and 12 total cancer cases detected in 82 patients in the intervention and control arms, respectively, in the first year. Going by this annual accrual rate, in two years, there should be 26 cancer cases out of 1582 patients in the intervention arm and 24 cancer cases out of 164 patients in the control arm. Therefore, achieving the 23 cases required for statistical significance in the stage at diagnosis in each arm at the end of the 2-year study period is possible.

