#### Control arm

The control LGA is about 4 kilometers from OAUTHC which is the referral tertiary hospital in this study. There are radiological (including ultrasound, mammography, computerized tomography, and magnetic resonance imaging services), pathological and surgical specialty services for breast cancer within OAUTHC which is also the primary institution of the study’s principal and co-investigators in Nigeria. In the control LGA, awareness creation will follow a similar procedure as outlined above for the intervention LGA. No other intervention will take place in the control arm. Women will not be invited to participate in a screening program and there is no community-based imaging, biopsy, or navigation. Women are expected to present to the PHCs if they have breast complaints which is a routine practice. Management of patients with breast-related complaints will be based on the current standard of care which is a review by the CHNs who refer or clinically manage otherwise based on his/her assessment. Twice a month, research staff will visit the selected PHCs in the control LGA to obtain data on the number and records of breast-related cases seen at the PHCs and those referred to OAUTHC. Patients referred to OAUTHC for suspicion of breast cancer will be tracked to determine the stage at diagnosis and the timelines from presentation at the PHC to eventual treatment at OAUTHC. In addition, patients presenting directly to OAUTHC from the LGA based on self-referral will also be identified and their data obtained.

Although the control arm participants do not have intervention provided in their LGA, they however get same workup, management and are navigated along the same pathway as the intervention arm participants once they present in OAUTHC for screening and diagnostic evaluation.

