**Fig 4 pone.0284341.g004:**
[figure not shown]
Outcome measures in the control and intervention communities.

Primary outcome measures.

Stage at presentation: This will be determined using both clinical and radiological assessment to determine the TNM stage among those with histopathologically confirmed breast cancer. It is expected that the number of patients with late-stage disease may be high at the outset, but this is expected to reduce as screening progresses in the intervention arm. Therefore, besides the absolute number of cases per stage, the pattern of presentation over time will also be assessed to determine if there is a decline in the number of late-stage cases between the prevalence and incidence rounds of screening. Cases of breast cancer from the intervention and control arms will be tracked both at the PHCs and OAUTHC. The stage and pattern of presentation of cases from the two arms will be compared.

Secondary outcome measures.

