A descriptive analysis of the data will be done at 1.5 years for the retention rate and abnormal call rate to inform our decision for future investigations. The rate of late-stage diagnosis will be estimated on a yearly basis. However, no stopping rules will be employed. This estimation will purely serve the purpose of detecting any difference in the annual trends of the stage of diagnosis over time between the intervention and control arms.

The initial findings for the subset of women who undergo a second round of screening will be examined to identify the stage of presentation in this group of women if diagnosed during the second round. Given in our setting ~80% of patients with breast cancer present in stages 3 and 4, we expect to see a trend toward earlier stage of presentation (stages 0, 1 and 2) in women undergoing repeat breast evaluation.

The 2-year study period is enough to generate adequate data to measure the participation rate and difference in stage at diagnosis between the study arms, as elaborated in the sample size calculation of the cancer cases. In addition, this study will provide a groundwork for exploring the difference in CDR between the 2 modalities (CBE and enhanced CBE) and the time to treatment, generating data to guide future studies in our population.

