### Statistical analyses

All data entered into the REDCap database will be exported as a dataset into R 4.2. Sociodemographic characteristics of the participants will be assessed using medians and interquartile ranges (IQR) for continuous variables and counts and percentages for categorical variables. Participation rate, retention rate, abnormal call rate, rate of late-stage diagnosis, and CDR will be reported as proportions with 95% exact confidence intervals. As for late-stage diagnosis, stage 4 cancers will be considered late-stage. The above-mentioned metrics will be compared between the intervention and control arms using Chi-square tests or Fisher’s exact test. The time intervals from presentation to treatment will be reported using medians and IQR and will be compared between the intervention and control arms using the Wilcoxon rank-sum test. The rate of late-stage diagnosis will be estimated and compared between the intervention and control arms on a yearly basis, starting from baseline, to assess if the intervention arm shows betterment in this rate consistently. Bonferroni correction for type I error will be implemented (α* = 0.0167) for this comparison. A logistic regression analysis which accounts for the ward (random effect) in which the patient was examined will also be performed with late-stage diagnosis as the dependent variable and time of screening, the interaction between the allocated groups (intervention and control arms), and time of screening as the independent variables. For all statistical comparisons (other than the one mentioned immediately above), the type I error rate (α) will be set to 0.05. All statistical analyses will be conducted using R 4.2 software [24]. Sample size calculations were done using the clinfun package of the R 4.2 software [25].

We do not anticipate any missing data due to loss of follow-up because the research team will make every effort to retain recruited participants. However, if missing data issues do arise, we will implement multiple imputation techniques, which impute missing data under the missing at random (MAR) assumption. Sensitivity analysis of the findings after multiple imputations will thereby be performed and these findings will be compared to those obtained from complete case analyses.

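### A fall in the number of late-stage cases between screening rounds is expected without any benefit, so it should not count as evidence of programme impact

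*Protocol article*

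**What the plan says.** The protocol article, under Primary outcome measures, names stage at presentation as the primary outcome. It expects many late-stage patients at the start and says that "this is expected to reduce as screening progresses in the intervention arm". It therefore adds to the count of cases per stage an assessment of the pattern over time, "to determine if there is a decline in the number of late-stage cases between the prevalence and incidence rounds of screening". No denominator is attached and no allowance is made for prevalent cancers already found. The same paragraph then says: "The stage and pattern of presentation of cases from the two arms will be compared".

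Program evaluation and outcome measures introduces these outcomes as the metrics by which the programme's impact will be assessed. Later in that section, on the women who have a second round, the authors write that "we expect to see a trend toward earlier stage of presentation (stages 0, 1 and 2) in women undergoing repeat breast evaluation".

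Three other statements bear on the point:

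- In the Control arm section: "Women will not be invited to participate in a screening program".
- In Statistical analyses, "stage 4 cancers will be considered late-stage". That section compares the rate of late-stage diagnosis between arms each year and adds a logistic model with a group-by-time interaction.
- In Sample size of cases, the powered comparison is the proportion at stage IV: "there were 7 (7/12, 58.3%) and 2 (2/13, 15.38%) stage IV cancers in the control and intervention arms respectively".

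**The concern.** The first round of a new programme finds cancers that have built up over years. Here it includes symptomatic women with obvious lesions. The annual repeat is scheduled for women who were negative on clinical breast exam and iBE, so the second round has fewer women, and most of its cancers must be new since the first. The number of late-stage cases should then drop sharply even if no cancer is diagnosed at an earlier stage than before.

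A drop in that number is nevertheless one of the things the primary outcome looks for, and the text attributes the expected drop to the progress of screening. Read that way, an artefact of having rounds could be taken for down-staging. The control arm offers no parallel fall to subtract, because it has no rounds.

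**Working it through.** **The plan's own figure.** The passage on rounds gives no number. The related figure is 23 cases per arm for 7/12 = 58.3% against 2/13 = 15.38% stage IV, with 80% power and alpha 0.05. Two-sided Fisher exact power is 78.6% at 22 per arm and 81.4% at 23, so 23 is reproduced. It concerns the between-arm proportion, not the count by round.

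**Inputs from the protocol article**
- First-year yield in the intervention arm: 13/791 = 1.64% (Sample size of cases). The anticipated detection rate is 3.5%.
- Cohort sizes: 791 in year one, 1,582 projected over two years, 4,100 planned.
- Stage IV share: 2/13 = 15.38%, held the same in both rounds, so no stage shift.
- Incidence: the Introduction describes breast cancer "with an incidence of 52/100,000".

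**Assumptions**
- The incidence is annual and the interval between rounds is one year.
- A multiplier m of 1 to 5 applies for the age range.
- Retention r is 70-100%; the article gives no expected figure.
- The two counts are independent Poisson variables.

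**Yield against incidence.** 1.64%/0.052% = 32 and 3.5%/0.052% = 67. With m = 3 to 5 the ratio is still about 6 (32/5) to 22 (67/3).

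**Expected stage IV counts**
- Round one: N × yield × 2/13.
- Round two: N × r × m × 0.00052 × 2/13.
- For 791 women, round one is 13 × 2/13 = 2.0.
- Round two is lowest at 791 × 0.7 × 0.00052 × 2/13 = 0.044 and highest at 791 × 5 × 0.00052 × 2/13 = 0.316.
- The smallest expected fall in these scenarios is 1 − 0.316/2.0 = 84%. The largest, at 4,100 women and 3.5%, is 1 − 0.23/22.1 = 99%.

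**Chance of a fall.** With X and Y the round-one and round-two counts, P(Y < X) is the sum over k of P(Y = k) × P(X > k).

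| Women, yield | Cancers, round 1 → 2 | Stage IV, round 1 → 2 | P(fall) |
|---|---|---|---|
| 791, 1.64% | 13 → 0.3-2.1 | 2.0 → 0.04-0.32 | 0.78-0.85 |
| 1,582, 1.64% | 26 → 0.6-4.1 | 4.0 → 0.09-0.63 | 0.92-0.97 |
| 4,100, 3.5% | 143.5 → 1.5-10.7 | 22.1 → 0.23-1.64 | above 0.999 |
| 4,100, 1.64% | 67.4 → 1.5-10.7 | 10.4 → 0.23-1.64 | about 0.995 to 0.9999 |

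In the smallest cohort the probability is limited because round one itself has no stage IV case with probability exp(−2.0) = 0.135, and then no fall is possible.

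**Sensitivity**
- *Stages III-IV counted as late, at 80% of cases:* P(fall) is about 0.995 or higher in every scenario.
- *Incomplete retention alone:* with 70% returning and no depletion, the expected count still falls by 30%, because a count has no denominator.
- *Cancers missed in round one:* the Introduction quotes 92% sensitivity (95% CI 77-98) for suspicious lesions with iBE plus clinical exam. If this applies to cancers, all missed ones surface in round two and m = 3, the expected fall is 82-87% and P(fall) is 0.77, 0.91 and above 0.999 for 791, 1,582 and 4,100 (at 3.5%) women.
- *Sensitivity of 77%:* in the 791 cohort the carry-over is 13 × 0.23/0.77 = 3.9 cancers. With 1.2 new ones that makes 5.1 against 13, an expected fall of about 61%.

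**The case against.** The best defence is that nothing formal hangs on this count. The pattern over time is an additional assessment with no test, threshold or success claim. The sample size rests on the between-arm proportion at stage IV, and the yearly comparisons and the interaction model also use proportions of cases. The second-round trend is an expectation about a subset, not a hypothesis test. This stands. A reader might infer that the primary analysis is invalid, or that the fall will be reported as proof of down-staging; the article supports neither. It does still place the count inside the primary outcome and call the outcomes measures of impact.

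The second defence concerns size. A reader might infer that a fall is almost certain whatever the programme does. For 791 women that is too strong when both counts are random. A reader might also infer that round two will hold about one cancer at most. That holds only for 791 women at low multipliers and with no missed cancers. The article intends all accrued participants to get a second screen, which would mean more women and more cancers.

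Third, the 13 in 791 come from a mixed symptomatic and asymptomatic group, so they are not a pure screening-round yield. This makes the exact ratio uncertain. It does not reverse the direction, since symptomatic prevalent cases inflate round one.

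Finally, the yearly between-arm analyses might seem to repair the problem. They do so only in part, because only the intervention arm has a prevalence bulge followed by depletion.

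**Conclusion.** The point holds for the within-arm count. With no change in stage mix, the expected number of stage IV cases falls by about 84-99% from the first round to the second. The probability of seeing a fall rises from about 0.78-0.85 (791 women) through 0.92-0.97 (1,582) to above 0.999 (4,100 at the anticipated 3.5%). A fall therefore says little or nothing about benefit.

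The figures rest on reading the incidence as annual, on the 1- to 5-fold age multiplier, on 70-100% retention and on Poisson counts. Allowing for missed cancers weakens the fall but does not remove it. The comparison of stage IV proportions between arms, on which the trial is powered, is outside this finding.

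**What to change.** 1. Under Primary outcome measures, state that the between-round change in the number of late-stage cases is descriptive only and is not evidence of impact.
2. List second-round cancers by stage, with the number of women rescreened. Do not treat the expected trend toward earlier stages among repeat attenders as evidence of impact: 0.3 to 2.1 cancers are expected there among 791 women and 0.6 to 4.1 among 1,582.
3. Add, for each arm, the cumulative two-year number of late-stage cases per 1,000 eligible residents aged 40-70, counting screen-detected, between-round and self-referred cases. Restrict cases to the wards and ages that the denominator covers. The article gives about 5,800 and 4,500 women aged 40-70 in the selected wards, and no denominator for symptomatic women aged 30-39.
4. Do not judge the programme by the between-arm difference in the change from year one to year two. Expressing cases per resident does not remove the bulge and depletion that only the intervention arm has.

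The cost is a change of wording and a little more analysis. Cases are already to be tracked at the health centres and the referral hospital. The drawback is reliance on estimated population denominators.

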#### Screening and diagnostic evaluation schedule in the intervention arm

In the intervention arm, consecutive consenting asymptomatic (40–70 years) and symptomatic (30–70 years) women will undergo screening and diagnostic evaluations respectively. Asymptomatic women (age 40–70 years) presenting for screening at designated PHCs will be evaluated by trained CHNs. Evaluation will entail a focused breast history, CBE, and iBE. Women with positive findings on CBE or iBE will be scheduled for another visit to have breast imaging and if indicated a breast biopsy. Women with negative findings on CBE and iBE will be scheduled for a similar repeat annual evaluation. Women will, however, be told to return at any time if any abnormality is noticed before their scheduled visit. Every woman who is screened will be given a breast health card (pink card) containing her name, contact information, a summary of findings on evaluation, and the date of the next examination. A duplicate copy of the breast card will be kept at the health centre for reference and follow-up. In addition to the breast health card, a detailed record of CBE and iBE findings for each patient will be kept by the PHC Nurse.

Symptomatic women (age 30–70 years) without an obvious lesion will be evaluated like the asymptomatic population, with focused breast history, CBE, and iBE. Those with positive findings will progress to imaging while those with negative findings will be scheduled for repeat evaluation on a short-term basis (one month). If symptoms persist at the time of the next evaluation, they will progress to imaging regardless of CBE and iBE findings.

Symptomatic women (age 30–70 years) with obvious breast lesion(s) will undergo focused breast history and CBE examination and will be scheduled to have imaging evaluation and breast biopsy if indicated (Fig 3).

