Participation rate: This will be determined by calculating the percentage of women screened/evaluated of the total number of eligible women based on census data. A participation rate of 70% will be considered satisfactory in the intervention arm. The number of screened/evaluated women in the intervention and control arms will also be compared.Cancer detection rate (CDR): This refers to the number of histopathologically diagnosed cases of breast cancer per 1,000 evaluated populations in both screening and diagnostic groups. This will be compared between the control and intervention arms.Timeline from presentation to treatment: The time interval between presentation for breast evaluation and treatment in OAUTHC of the cases in the two arms will be compared.Retention rate: The retention rate refers to the number of women who return for repeat annual screening of the total initial number of women initially screened in the first year. A repeat screening within a year and a half will be considered acceptable for this two-year study. To ensure all accrued participants get their second screen, we will follow them up beyond the initial study period as needed.Abnormal call rate: This is defined as the number of women with abnormalities detected on iBE and/or CBE requiring further evaluation either by imaging with or without biopsy out of the total number of asymptomatic and symptomatic without an obvious lesion participating in the study. There are 2 groups of participants (diagnostic and screening) in each of the 2 arms (intervention and control). The screening group constitutes the asymptomatic participants while the diagnostic group constitutes the symptomatic participants. The interventions in this study include enhanced CBE (CBE + iBE), community-based diagnostic evaluation (with portable ultrasound and mobile mammography), and biopsy (if warranted). To evaluate which of CBE and enhanced CBE was of greatest value, another layer of analysis will be provided to address this question by comparing the concordance of the two with imaging which is the gold standard. This study also provides an additional opportunity to evaluate the iBE device.

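### The retention rate is divided by every woman screened in year one, but an annual repeat is stated only for asymptomatic women negative on CBE and iBE, so women not due to return can be counted as not retained

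*Protocol article*

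**What the plan says.** Retention is a secondary outcome in the protocol article, defined under the secondary outcome measures as "the number of women who return for repeat annual screening of the total initial number of women initially screened in the first year". No group is removed from the denominator. The same entry sets the time window, "A repeat screening within a year and a half will be considered acceptable for this two-year study", and adds an intention: "To ensure all accrued participants get their second screen, we will follow them up beyond the initial study period as needed".

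The section on the screening and diagnostic evaluation schedule in the intervention arm says what follows each first examination:

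- Asymptomatic, negative on both tests: "Women with negative findings on CBE and iBE will be scheduled for a similar repeat annual evaluation".
- Asymptomatic, positive on either test: "Women with positive findings on CBE or iBE will be scheduled for another visit to have breast imaging and if indicated a breast biopsy". No later annual visit is stated.
- Symptomatic without an obvious lesion: imaging if positive. If negative, a repeat after one month, then imaging if symptoms persist.
- Symptomatic with an obvious lesion: imaging, and biopsy if indicated.

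Under patient navigation and follow-up, women with histologically confirmed cancer are sent to the breast clinic at the referral hospital. Each screened woman receives a card showing "a summary of findings on evaluation, and the date of the next examination".

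The statistical analyses section reports retention as a proportion with a 95% exact confidence interval and lists it among the metrics to be compared between arms. A descriptive look at retention and the abnormal call rate is planned at 1.5 years.

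**The concern.** A retention rate should answer one question: of the women who were due back, how many came? Here the group counted in the denominator is not the group that the schedule sends back. The denominator holds everyone screened in the first year. The event counted in the numerator, a repeat annual screen, is stated as scheduled only for asymptomatic women with two negative tests.

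A woman whose cancer was found at the first round is the programme's intended success, yet she is scored as not retained. The same happens to any other woman who is not put back on the annual schedule. The 18-month window does not cure this, because a woman who was never due stays in the denominator after the window closes.

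At stake is how a predefined programme metric is read. The 1.5-year look is meant to inform later investigations, and a shortfall produced by the definition could be taken for loss of women.

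**Working it through.** The protocol gives no retention target, expected value or observed value, so there is no stated figure to reproduce.

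**Inputs**

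- Cancer fraction *c*, observed: "13 total cancer cases detected in 791 patients" in the intervention arm in the first year (Sample size of cases), so *c* = 13/791 = 1.64%.
- Cancer fraction *c*, anticipated: a detection rate of at least 3.5% (same section), so *c* = 3.5%.
- Share of first examinations that are positive, *a*: the abnormal call rate is defined but no value is given. Assumed values: 5%, 10% and 20%.
- Return rate among women due for a repeat, *r*: not given. 80% is used as an illustration.

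**Formula**

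Assume that cancers are found among women with a positive examination, are diagnosed before the annual repeat falls due, and do not return for screening. Let *p* be the return rate among women with a positive examination and no cancer. The rate as defined is then

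reported retention = (1 − *a*)·*r* + (*a* − *c*)·*p*.

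**Reading 1: only diagnosed cancers do not return (*p* = *r*).** The formula reduces to (1 − *c*)·*r*, which does not depend on *a*.

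- *c* = 13/791: ceiling 1 − 0.0164 = 98.4%; at *r* = 80%, 0.80 × 0.9836 = 78.7%.
- *c* = 3.5%: ceiling 1 − 0.035 = 96.5%; at *r* = 80%, 0.80 × 0.965 = 77.2%.
- On the projected 4,100 women, that is 4,100 × 13/791 ≈ 67, or 4,100 × 0.035 ≈ 144, who cannot count as retained.

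**Reading 2: no woman with a positive examination returns (*p* = 0).** The formula reduces to (1 − *a*)·*r*.

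| Assumed *a* | Ceiling | Reported at *r* = 80% |
|---|---|---|
| 5% | 95% | 0.80 × 0.95 = 76% |
| 10% | 90% | 0.80 × 0.90 = 72% |
| 20% | 80% | 0.80 × 0.80 = 64% |

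Reading 2 needs both an assumed positive rate and a non-return rule that the documents do not contain.

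**Symptomatic women with negative findings.** They are rescheduled at one month and no annual visit is stated. If they count as screened and are not later moved to the annual schedule, their share comes off the ceiling too. The documents do not give that share.

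**With the denominator limited to women due for the repeat**, the reported rate equals *r* and can reach 100%.

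**The case against.** The strongest defence is that the schedule is silent about later visits and does not exclude anyone. It gives the next step after a positive examination and never says that a woman with benign imaging leaves annual screening. The intention that all accrued participants get a second screen, and the card with a next-examination date, both suggest that she is expected back. The pathway figure is not shown and may settle it. Nor is the numerator limited to women who were negative at first.

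Much of this stands. A reader might infer that every positive examination is scored as a failure to return, that the ceiling is one minus the abnormal call rate, and that the two metrics are therefore mechanically tied. The documents do not support this. A woman with a positive examination and no cancer who returns within the window counts as retained, and if such women return like the others the call rate drops out of the formula.

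Two further points limit the size. The secondary outcomes section describes the screening group as the asymptomatic participants. If women screened means only them, symptomatic women fall outside the denominator, while both cancer rates used above come from mixed populations. Also, retention is secondary and has no threshold, unlike the 70% set for participation.

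The defence does not remove the mismatch. The card date may be the imaging visit, so it does not show who is due annually. The statement about all participants takes in women whose cancers the navigation section sends to the breast clinic. The denominator is a stated rule without exclusions, so applying it as written counts those women as not retained.

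**Conclusion.** The point holds in limited form. The retention denominator does not match the women for whom an annual repeat is stated, and the two sections disagree on who should have a second screen. The clear effect is from diagnosed cancers: a ceiling of about 98.4% or 96.5%, and a true 80% return reported as about 78.7% or 77.2%. This assumes that women with diagnosed cancer do not return for screening and that cancer rates from mixed symptomatic and screening populations apply; among screened women alone the loss may differ.

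Reported values of 76%, 72% or 64% would arise only if no woman with a positive examination returned, at assumed positive rates of 5%, 10% or 20%. They show how far the figure could move while the rule is unsettled and are not an estimate of the bias. The primary outcome, stage at diagnosis, and its power are unaffected.

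**What to change.** 1. Reconcile the evaluation schedule with the retention definition by stating which women are due for the annual repeat. This must cover women with a positive examination and no cancer, and symptomatic women with negative findings. Which recall rule applies is for the investigators to state; this review proposes none.
2. Define the retention denominator as first-year women due for that repeat, excluding deaths and cancers diagnosed before it falls due.
3. Apply the same rule to the numerator, so that only women in the denominator can count as returned.
4. Report the excluded groups separately, with counts, so that the total screened in year one can still be accounted for.

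The cost is wording. First-examination, imaging and pathology results are already on the case report form, and the next-examination date is on the breast health card, of which the health centre keeps a duplicate. The sample size and primary analysis do not change.
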